### Participants

The study sample will consist of both gender Portuguese participants, over 18 years, with CLBP lasting three months or longer and with an intensity of 3 or higher on the visual analogue scale (VAS) at rest. Individuals who refuse to participate or do not provide informed consent will be excluded, as well as those with pain radiating to the lower limb, recent pregnancy or childbirth (less than 8 weeks ago) [50], ongoing physical therapy treatments, severe rheumatological, neurological, neoplastic, cardiovascular diseases, or other conditions that could prevent full participation in the intervention, a history of spinal surgery, inflammatory, infectious, or malignant spinal diseases, and psychiatric disorders that may affect adherence and symptom assessment [41–43].

The sample will be randomly divided into two groups: the experimental group, which will undergo the aquatic and land-exercise program (ALG), and the control group, which will perform the aquatic-exercise program (AG).

The required sample size was calculated using the G*Power software (3.1.9.4; Heinrich Heine University Düsseldorf, DE), based on a study with 65 participants by Dundar *et al*. [42] and corroborated by other studies [51–53]. The aim was to detect differences in pain intensity (VAS) between the aquatic exercise program group and the control group (land exercise), with an effect size of 1.079, α=0.05, and a power of 80%. The total sample size needed to achieve the objective will be 30 participants (15 in each group).

Thus, the study should start with an additional 15% of the planned sample size for each group to account for potential dropouts and as well as adopt cognitive-behavioral strategies to reduce dropout rates, such as setting flexible and participant-driven goals or providing positive and individualized feedback [54,55].

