#### Randomization and Blinding.

Participants who meet eligibility criteria will be given an alphanumeric code to maintain data confidentiality and anonymity. Participants will be randomly assigned to either ALG or AG, with a 1:1 allocation. Randomization will be performed by the principal investigator using a block randomization method generated by a computer program to ensure equal sample sizes in both groups. The block size will not be disclosed to maintain concealment. Participants will be informed of their group allocation (ALG or AG) via telephone contact. The principal investigator will not be actively involved in the intervention, data collection or data analysis. Randomization will only be known to the physiotherapists responsible for the intervention and the principal investigator. The examiner will evaluate participants before the intervention and after 8 weeks of intervention, ensuring blinding to group allocation, and participants will be asked not to disclose this information to the examiner. Each intervention will have a physiotherapist responsible for its execution, who will be instructed not to reveal participants’ group allocation to other research team members. Both data collector and data analyst will be unaware of the participants’ group distribution and will also be considered blinded. Only the principal investigator will have full knowledge of the entire research flow.

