### Statistical analysis

An inspection of the data will be made for missing values or univariate outliers. A priori power analysis through ${\text{G}}^{*}$Power (3.1.9.7) [96] and ANOVA repeated measures, within-between interaction will be use to determine the required sample size considering the following input parameters: (effect size *f* = 0.4; α err prob = 0.05; statistical power = 0.95) [97]. Data analyses will be performed using SPSS Statistics version 29.0 (SPSS Inc., IBM Company, Chicago, Illinois, USA). Descriptive statistics (mean ± SD) will be performed for all variables in the analysis. Assuming data normality, a 2×3 within-between interaction factorial ANOVA will be applied for intra and inter group comparisons. To control for Type I errors, multiple comparisons will be adjusted using the Bonferroni correction (i.e., alpha level divided by the number of tests) as suggested by several authors (e.g., Ho, 2014) [98].The magnitude of the global effect size will be calculated using Cohen’s effect size. The Cohen’s *d* effect size is categorized according to the following criteria: *d* = < 0.20 (small), 0.21–0.79 (medium) and > 0.80 (large) [99–101]. Significance level set at ρ
≤ 0.05. Full statistical analysis and results are expected to be completed in May 2025.

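### Single-step Bonferroni is valid, but Holm's step-down gives the same familywise error control and never rejects less: a cheap, minor improvement

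*Protocol article*

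**What the plan says.** The Statistical analysis section of the protocol article plans that "a 2×3 within-between interaction factorial ANOVA will be applied for intra and inter group comparisons". The next sentence gives the purpose, "To control for Type I errors", and the method: "multiple comparisons will be adjusted using the Bonferroni correction (i.e., alpha level divided by the number of tests"). It supports the choice with a citation and sets the overall level at 0.05 ("Significance level set at ρ" ≤ 0.05). The number of tests is not stated.

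The sample size stands in the Participants section. It is a single comparison of pain on the VAS "with an effect size of 1.079, α=0.05, and a power of 80" per cent, leading to: "The total sample size needed to achieve the objective will be 30 participants (15 in each group"). Allocation is "with a 1:1 allocation". VAS, ODI and SF-36 are all listed as primary outcomes. The hypothesis at the end of the Introduction expects benefit on pain, disability and quality of life together.

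**The concern.** Dividing alpha by the number of tests fixes one particular procedure, and another one dominates it. Holm orders the p-values, compares the smallest with alpha/m, the next with alpha/(m−1), and so on, and stops at the first failure. It meets the plan's stated aim equally well and can only add rejections.

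What is at stake is power on the second and later outcomes. That is relevant here because the hypothesis covers several outcomes and the trial has about 15 participants per arm. The validity of the conclusions is not at stake, and neither is the chance of finding at least one effect.

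**Working it through.** **Inputs from the protocol.** Effect size 1.079, alpha 0.05, 80% power and 15 per group (Participants); 1:1 allocation (Randomization and Blinding); Bonferroni at overall 0.05 (Statistical analysis).

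**Assumptions.** The protocol gives neither the number of tests m nor the correlation between them. I took m = 3, 5 and 13 and correlation 0 and 0.5, with two-sided tests. Between-group t-tests at one time point stand in for the planned comparisons.

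**Step 1: the plan's own figure.** For a two-sample t-test with n per group, df = 2n − 2 and the noncentrality is d√(n/2). At n = 15 this is 1.079 × √7.5 = 2.955 with 28 df. Two-sided power at 0.05 is 81.4%, and 15 is the smallest n reaching 80%. The stated total of 30 reproduces.

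**Step 2: one test at the Bonferroni threshold, same n and d.**

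| m | 0.05/m | power |
|---|---|---|
| 1 | 0.05 | 81.4% |
| 3 | 0.0167 | 65.9% |
| 5 | 0.0100 | 58.1% |
| 13 | 0.0038 | 43.9% |

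**Step 3: why Holm dominates.** For m = 3 the Bonferroni thresholds are 0.0167, 0.0167, 0.0167. Holm's, from the smallest p-value up, are 0.05/3 = 0.0167, 0.05/2 = 0.025 and 0.05/1 = 0.05. No Holm threshold is below 0.05/m, so every p-value that passes Bonferroni also passes Holm.

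Error control: suppose m₀ null hypotheses are true. The true null with the smallest p-value has rank at most m − m₀ + 1, so rejecting any true null requires one of the m₀ p-values to be at most 0.05/m₀. By the union bound that has probability at most m₀ × 0.05/m₀ = 0.05, whatever the dependence.

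**Step 4: size of the gain.** Simulated trials, 15 per arm, correlation 0.5 (20,000 runs; 8,000 for m = 13). Power is the average per real effect.

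| m | true effects | Bonferroni | Holm | at least one rejection (both) |
|---|---|---|---|---|
| 3 | all 1.079 | 65.5% | 74.1% | 87.7% |
| 3 | all 0.5 | 13.6% | 16.0% | 29.1% |
| 3 | one 1.079, rest 0 | 65.4% | 65.5% | 66.6% |
| 5 | all 1.079 | 58.1% | 69.2% | 89.4% |
| 5 | all 0.5 | 9.8% | 11.7% | 29.7% |
| 5 | one 1.079, rest 0 | 58.1% | 58.2% | 59.7% |
| 13 | all 1.079 | 43.7% | 55.7% | 91.0% |

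The last column is the same for both methods because Holm's first step is the Bonferroni step.

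A separate run of 40,000 trials (m = 3, correlation 0.5) agrees. With all effects 1.079, power per test goes from 65.8% to 74.4%, and the chance that all three tests are significant from 41% to 61%. With unequal effects of 1.079, 0.8 and 0.5, power goes from 66/38/14% to 68/44/22%.

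**Step 5: familywise error with no real effects.** For m = 3 it is 4.9% at correlation 0 and 4.4% at 0.5; for m = 5, 4.8% and 4.4%; for m = 13, 5.3% and 4.1%. The two methods give identical values. The 5.3% rests on 8,000 runs, with standard error √(0.05 × 0.95/8000) = 0.24 points, so it is compatible with 5%.

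**Step 6: role of correlation (m = 3).** With all effects 1.079, the gain per test falls from about 10 points at correlation 0 to about 8 at 0.7. With all effects 0.5 it rises, from 1.2 points at correlation 0 to 2.4 at 0.5. The gain comes from several effects being real and does not need correlated outcomes.

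**The case against.** The strongest reply is that nothing here is wrong. Bonferroni is standard, it is prespecified with a supporting citation, it controls familywise error for any number of tests and any dependence, and it has simple matching simultaneous intervals. The protocol claims no optimal power, and nothing elsewhere in it contradicts the choice. All of that stands, and it is why the point is an improvement and not an error.

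The large gains also rest on a generous assumption. The effect of 1.079 is given only for VAS pain, for aquatic against land exercise. Here both arms receive the aquatic programme and one adds a weekly land session. The Discussion reports no significant VAS difference in the study on which the calculation was based, and says the direction of the result cannot be projected. At an effect of 0.5 the gain is 2 to 3 points for 3 tests. This stands too.

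The Bonferroni sentence directly follows the ANOVA, so it may cover only post hoc contrasts within each outcome. That affects the figures in Step 4, which compare groups across outcomes. It does not affect the dominance of Holm, which holds for any set of tests.

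A reader might infer that a trial of 30 cannot afford Bonferroni, or that correlated outcomes make the loss worst. Neither is supported. The chance of any rejection is identical under both methods, and correlation has no consistent effect on the gain. Nor does Holm answer the separate question of a sample size set at unadjusted alpha: its first threshold is the same, so the fall from 81.4% to 65.9% at 0.05/3 remains there.

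**Conclusion.** The point holds as a minor, cheap improvement. The stated rule is valid but uniformly dominated by Holm for the purpose the plan itself gives. With 15 per arm, 3 tests and correlation 0.5, Holm adds about 8 to 9 points of power per test if every effect is 1.079, about 2 points if every effect is 0.5, and almost nothing if only one effect is real. The dominance needs no assumption about effects or dependence. The sizes rest on two-sided between-group t-tests and on an assumed number of tests, since the protocol gives none.

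**What to change.** In the Statistical analysis section, replace the Bonferroni correction and its bracketed definition with the Holm step-down adjustment. Apply it to the same set of tests that Bonferroni would have covered, and write that set down before the analyst sees results by group. Without that list neither procedure can be carried out as stated. Report Holm-adjusted p-values against 0.05, with ordinary 95% confidence intervals for the estimates.

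The cost is one sentence and no extra participants. Two small downsides should be accepted openly. Holm has no simple matching simultaneous intervals, although the plan states none. The adjusted p-values must also be computed from the unadjusted ones outside the SPSS post hoc menu, which a spreadsheet can do.

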#### Primary outcomes

**Visual Analogue Scale (VAS).** The VAS is a unidimensional measure of pain intensity used to track its progression over time. This instrument consists of a 100-millimeter line, presented either vertically or horizontally, with an initial value of 0 indicating “No Pain" and an end value of 10 representing “Worst Pain." Participants are asked to mark a perpendicular line on the scale that corresponds to their level of pain. The scale is recorded on a single-use sheet of paper, and the value is obtained by measuring the distance from the origin (0) to the mark [70]. The VAS is a validated tool for assessing the intensity of CLBP, with moderate to strong construct validity (0.50–0.81), moderate to excellent test-retest reliability [Intraclass Correlation Coefficient (ICC) = 0.49–0.90], and a standard error of measurement (SEm) of 0.1% [71]. Additionally, the minimal clinically important difference (MCID) for this instrument is 20mm for CLBP [72].

**Oswestry Disability Index – version 2.0 (ODI).** The ODI is a tool used to measure and assess the disability caused by low back pain. It consists of 10 questions, each rated on a Likert scale from 0 to 5, where 0 represents no dysfunction and 5 represents the highest level of dysfunction. The final score is expressed as a percentage, indicating the level of disability experienced by the individual with low back pain: 0%–20% (minimal disability); 21%–40% (moderate disability); 41%–60% (severe disability); 61%–80% (very severe disability); 81%–100% (exaggerated symptoms) [73,74]. This instrument has been translated and validated for the Portuguese population, showing a good correlation with the MOS Short Form Health Survey 36 (r=−0.59 to –0.75) and excellent internal consistency (Cronbach’s α = 0.95) and reproducibility (ICC = 0.90) [75,76]. The MCID for this questionnaire was established at 10% [72,77].

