**MOS Short Form Health Survey 36 Item v2 (SF-36 v2).** The SF-36 v2 questionnaire is an assessment tool primarily designed to measure and evaluate the health status and quality of life of populations and individuals, whether they have health conditions or not. It consists of 36 items, rated on a scale from 1 to 5 (Likert scale). The questionnaire is divided into 8 dimensions (physical functioning, physical role limitations, bodily pain, general health perceptions, energy/vitality, social functioning, emotional role limitations and mental health), which can be grouped into two components (physical health and mental health). Scores for each dimension are presented on a positively oriented scale from 0 (worst health state) to 100 (best health state) [78]. The instrument was previously validated and translated for the Portuguese population, demonstrating good content validity (*r*>0.401) and moderate to excellent levels of internal consistency (Cronbach’s α = 0.60–0.87) and test-retest reliability (ICC = 0.45-0.84) across its various domains [79,80]. For this instrument, the MCID has been established at 6 for mental health and 14 for physical health [81].

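### The Cohen's d bands start 'medium' at 0.21 and apply to an undefined 'global' effect, so with 15 to 18 per group chance differences would often be described as medium effects

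*Protocol article*

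**What the plan says.** The Statistical analysis section of the protocol article plans a 2×3 ANOVA (group by time) with Bonferroni-adjusted comparisons. It then adds: "The magnitude of the global effect size will be calculated using" Cohen's effect size. Values up to 0.20 are called small, and the remaining bands are "0.21–0.79 (medium) and > 0.80 (large"). The section does not say which two means d compares, at which time point, or which SD divides the difference. Nor does it mention a confidence interval for d.

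The Participants section says the total sample "will be 30 participants (15 in each group"), planned "with an effect size of 1.079" on the VAS, with 15% added per group for dropout.

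The outcome descriptions give clinical thresholds. For the VAS, "the minimal clinically important difference (MCID) for this instrument is 20mm for CLBP". For the ODI, "The MCID for this questionnaire was established at 10" percent. For the SF-36, "the MCID has been established at 6 for mental health and 14 for physical health". The TSK-13 value is 5.5 points. The lumbar mobility test has only a minimal detectable difference of 1 cm.

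**The concern.** The conventional benchmarks mark the points at which an effect begins to count as small (0.2), medium (0.5) and large (0.8). The protocol turns 0.20 into the top of the small band. 'Medium' therefore starts at 0.21, 'small' includes zero, and one word covers a nearly fourfold range of effects.

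In a trial of about 30 people, the sampling error of d is larger than that lower cut-point. A label that begins at 0.21 will often be earned by chance. Readers of a small exercise trial tend to take a 'medium effect' as meaningful even beside a non-significant test, and the Discussion says the results are meant to inform practice and prescription.

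The undefined 'global' d adds a second difficulty. Cohen's d compares two means, and a group-by-time effect over three time points has no single such value. The analyst would have to choose a definition after the fact, and the choice changes how often a label is reached.

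**Working it through.** **Inputs from the protocol article.** 15 per group (Participants); 18 per group after the dropout allowance (15 × 1.15 = 17.25, rounded up); 1:1 allocation (Randomization and Blinding); α = 0.05 and the d bands (Statistical analysis). Sidedness is not stated, so two-sided is assumed.

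**The plan's own figure.** A two-sided two-sample t-test with d = 1.079, α = 0.05 and 80% power needs 15 per group (power 81.4%), 30 in total. This matches the plan. It shows that a between-group d with pooled SD is a sensible reading of the scale in use. The lower edge of 'medium' is 0.21/1.079 = 0.19 of the effect the trial was sized to detect.

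**Chance of a label with no true difference.** For n per group and pooled SD, d = t·√(2/n), with t on 2n − 2 degrees of freedom. So P(|d| ≥ c) = 2·P(T > c/√(2/n)).

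- n = 15: √(2/15) = 0.365; 0.21/0.365 = 0.575 on 28 df.
- n = 18: √(2/18) = 0.333; 0.21/0.333 = 0.630 on 34 df.

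| Event, no true effect | n = 15 | n = 18 |
|---|---|---|
| \|d\| ≥ 0.21 (medium or large under the plan) | 57.0% | 53.3% |
| of which favouring the combined programme | 28.5% | 26.6% |
| \|d\| ≥ 0.50 (conventional medium or more) | 18.2% | 14.3% |
| \|d\| ≥ 0.80 | 3.7% | 2.2% |

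Simulation with 200,000 trials per sample size gave the same 57.0% and 53.3%. With the Hedges small-sample correction the first row becomes 55.9% and 52.4%. If the 80% attendance exclusion cut the analysed sample to 12 per group, it would be 61.2%.

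**What the trial can distinguish from zero.** The smallest d significant at unadjusted two-sided 0.05 is t(0.975, 2n − 2)·√(2/n): 0.75 at n = 15 and 0.68 at n = 18. Most of the 'medium' band lies below that. The same 0.75 is the approximate 95% CI half-width at n = 15, so an estimate of 0.25 would be called medium with an interval of about −0.50 to 1.00.

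**Sensitivity to the definition of d.** With baseline/follow-up correlation ρ, normal approximation:

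- Difference in change over the raw SD: standard error √((2/n)·2(1 − ρ)). At ρ = 0.7 and n = 15 this is √(0.1333 × 0.6) = 0.283, giving P(|d| ≥ 0.21) = 46%; at n = 18 it is 42%. At ρ = 0.5 the figures are 57% and 53%.
- Baseline-adjusted difference over the raw SD: standard error √((2/n)(1 − ρ²)). At ρ = 0.7 the figures are 42% and 38%.
- d taken as 2f from the group-by-time interaction: 74% and 69%.

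The correlations are assumptions; the protocol gives none.

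**Native units.** If the VAS SD were 15 to 30 mm (an assumption), d = 0.21 would be 0.21 × 15 = 3 mm to 0.21 × 30 = 6 mm, against the cited MCID of 20 mm.

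**The case against.** **Inference does not rest on the labels.** A reader might infer that over half of null trials would claim an effect. The documents do not support that. Testing is by ANOVA with Bonferroni adjustment at 0.05, and the bands are descriptive. This stands: the problem is one of description.

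**The figure is conditional.** It applies to one contrast, counts both directions and assumes a pooled-SD between-group d. Some definitions bring it below half. This stands, and the figure should always be quoted with those conditions. It does not rescue the rule, because every definition tried still gives a high chance rate.

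**The MCIDs.** It is tempting to say that the trial ignores its own clinical thresholds. The article simply does not say how they will be used, and a condensed article may leave that to the full protocol or analysis plan. Their absence from the analysis section is not an error. The documents also do not say whether each value refers to individual change or to a group difference.

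**'Global' need not mean the interaction.** The section also plans comparisons within and between groups, where a two-mean d is valid. So it cannot be said that d is wrongly computed on the interaction, only that its target is undefined.

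**The gaps between bands** (around 0.20 to 0.21 and 0.79 to 0.80) are trivial.

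**Conventional bands do not remove sampling error.** At 15 per group, 59% of null contrasts would still pass 0.20. That is true, but they would be called small unless they also passed 0.50, and a confidence interval beside them shows the uncertainty.

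**Conclusion.** The concern holds as a matter of reporting. The protocol fixes a band that calls d 'medium' from 0.21, where 0.5 is conventional, and does not define the effect it labels. For a between-group pooled-SD d with no true difference, a single contrast would be called medium or large in about 57% of trials at 15 per group and 53% at 18, against 18% and 14% with a 0.5 cut-point. About half of each figure favours the combined programme. The rate depends on the standardiser, for example about 46% at 15 per group for a change-score difference over the raw SD with correlation 0.7. The error rate of the planned tests is unaffected.

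**What to change.** Make the difference between the combined-programme group (ALG) and the aquatic group (AG) in native units, at 8 weeks (M1) and at follow-up (M2), the main effect measure, each with its 95% CI. Discuss it alongside the MCIDs already cited for VAS, ODI, SF-36 and TSK-13, stating for each whether it refers to individual change or to a group difference. Treat the 1 cm mobility value as a minimal detectable difference, not a clinical threshold.

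If d is kept, name its contrast and standardiser, give its 95% CI, and use contiguous bands: below 0.2 negligible, 0.2 to below 0.5 small, 0.5 to below 0.8 medium, 0.8 and above large. Where an effect is called medium and its interval includes zero, say so in the same sentence.

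This needs no new data and no change to the planned tests. The cost is a little extra reporting and somewhat less favourable labels. It should be settled before the data are analysed.

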## Discussion

This study will investigate and compare the effectiveness of a water-based and land-based exercise program versus a solely water-based program on pain levels, functional disability, quality of life, lumbar mobility, and fear of movement in adults with CLBP. Additionally, an effort will be made to assess the effect of the cessation of exercise on the mentioned variables, 4 weeks after the end of the intervention. A minimum of 15 participants per group is expected to ensure the calculated sample power. However, a higher number of participants should be ensured, as it is known that approximately 50% of participants drop out within the first six months due to personal characteristics, environmental factors, or issues with the programs [55]. On the other hand, in order to maintain the methodological quality of the study, according to the Physiotherapy Evidence Database (PEDro) Scale, the variables should be measured at the end in more than 85% of the participants who were initially randomized [102].

Previously, an author conducted a RCT with 12 participants (6 in the experimental group and 6 in the control group) in which the effect of an aquatic exercise program (experimental) was compared with that of a land-based program (control) on the level of pain and mobility of the lumbar spine [41]. At the end of the interventions (6 weeks), no statistically significant differences were observed in pain (VAS) (ρ=0.523), nor in the lumbar spine mobility test (Modified-Modified Schober Test) (ρ=0.56). Another author also studied in a RCT the differences between a group of participants who engaged in an aquatic exercise program (experimental) and a group who engaged in a land-based program (control) with 65 individuals with LBP (32 in the experimental group and 33 in the control group) [42]. After 4 weeks of intervention, statistically significant differences were observed favoring the experimental intervention in the ODI score (ρ < 0.001) and in the physical function (ρ < 0.001) and physical performance (ρ < 0.001) domains of the SF-36 questionnaire. No statistically significant differences were found between the groups in rest pain, pain during movement, or nocturnal pain (VAS), in lumbar mobility test (Modified-Modified Schober Test), or in the remaining domains of the SF-36 questionnaire.

The study (RCT) with the most similar methodology was conducted with 66 participants (33 in each group) and aimed to examine the effect of an experimental aquatic and land-based exercise program compared to a control program of exclusively land-based (home-based) [43]. After two weeks of intervention, statistically significant differences were observed favoring the experimental intervention in pain: VAS at rest (ρ < 0.001), during exercise (ρ < 0.001), and overall in the lumbar spine (ρ < 0.001); in the ODI score (ρ = 0.045); and in the SF-36 domains of physical performance (ρ = 0.033), mental health (ρ = 0.021), pain (ρ = 0.014), and general health (ρ = 0.05). No statistically significant differences were found between the groups in the remaining domains of the SF-36 questionnaire or in the Modified-Modified Schober Test.

No study with a similar methodology has reported results for the TSK-13 questionnaire to date. Thus, it is challenging to predict the results of the study, as the methodologies differ and the sample sizes and intervention durations vary considerably among authors. It is not possible to project whether the group that will undertake the additional land-based exercise session will achieve better outcomes than the experimental group at the end of the intervention, in the studied variables. However, the variables most sensitive to the presented interventions appear to be pain, measured by VAS, functional disability measured by ODI, and some domains of the SF-36 related to pain and physical performance. These are likely to be the variables with the greatest variability at the end of the study. On the other hand, it is difficult to predict the trend of changes in the studied variables after 1 month of exercise cessation due to the lack of reference literature.

Thus, this study aims to provide implications for the practice and prescription of physical exercise and effective strategies that may contribute to potential benefits for individuals with LBP. Like all studies, this one will have some limitations: it will be impossible to fully control activities outside of the protocol, which may affect the studied variables either positively or negatively, and aquatic exercise limits the calculation of exercise intensity, which will be monitored only through perceived exertion.

